Both the benefits and drawbacks of their participation will be discussed with the participants. To avoid any misunderstandings, participants will be given written information about the consent before their enrolment. Potential volunteers will be chosen based on their primary complaints such as clinical anemia and family history. The blood sample will be drawn while the individual sits securely and in an aseptic setting. Two milliliters of venous blood will be collected in an ethylenediaminetetraacetic acid (EDTA) tube, gently mixed, and processed using a five-part automated hematology analyzer (Coulter) for complete blood count (CBC) testing and the estimation of RBC indices, including MCV, MCH, MCHC, and RDW. Based on various RBC indices and a histogram, the Beckman counter-analysis report will be examined to diagnose the kind of anemia. Simultaneously, a blood smear will be prepared in a Blue Star slide (75 mm length, 25 mm width, 1.35 mm thickness) from the given blood sample and allowed to dry. After that, staining will be performed using Leishman's stain and Leishman's buffer. The smear will next be examined under a microscope with an oil immersion lens (100×), and the findings will be recorded to make the morphological diagnosis of anemia. One pathologist will independently perform the morphological analysis to ensure accuracy and consistency. The PBS and cell counter methods will be used to collect the data, and the data will be compared and analyzed by using tests like the paired t-test and chi-squared test to draw a conclusion.

CBC

After the blood sample is collected in the EDTA tube, it will be sent to the pathology processing lab. The sample will be aligned in a cassette for processing. Then the cassette will be kept in the Beckman Coulter B1 (UniCel DxH 800). By using the principle of electrical impedance, results will be given by the machine, and this result will be used to analyze CBC and its relation with anemia. Based on various RBC indices and a histogram, the Beckman counter-analysis report will be examined to diagnose the kind of anemia.

PBS

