PBS provides valuable information for diagnosing anemia by examining minute variations in the morphology of blood cells. The procedure is as follows: A small layer of blood will form on the smear. After allowing it to air-dry, place them on a dyeing rack. After pouring Leishman's dye drop by drop on the slide, set it for two minutes. This makes it possible to calculate peripheral blood film (PBF) in methyl alcohol. After pouring twice as much buffering water on the slide by drops, let it rest for eight minutes before washing it for a minute or two. After allowing it to air-dry, examine it using a microscope's oil immersion lens. After that, the smear will be examined under a microscope with an oil immersion lens (100×) to determine the morphological diagnosis of anemia, and the results will be recorded. Abnormalities in the size, shape, or color of RBCs (anisocytosis, poikilocytosis, hypochromia) are valuable assets in the distinction between the various types of anemia.

Sample size

The sample size was calculated using Cochran's formula by considering the proportion of the estimated prevalence of anemia (p=28.6%) from the reference article and the estimation error (d = 5%); hence, calculating the total number of anemic patients visiting the hospital, the population size (N) of 314 patients is needed in the study.

The sample size for this study was determined using Cochran's formula. The formula used is as follows: n>=𝑍²1-𝛼/₂×(1−𝑝)/E2. Here, 𝑍²1-𝛼/₂ is the level of significance at 5%, i.e., confidence interval is equal to 1.96, p is equal to 28.6% or 0.286, and E (error of margin) is equal to 5% or 0.05. Thus, n>=1.96^2^×0.286×(1−0.286)/(0.05)², resulting in 313.7 or 314 patients needed in the study [14].

Outcome measures

Under a microscope, we will examine the RBCs in anemic patients for abnormalities such as variations in size, shape, and color, which are indicative of different types of anemia. However, CBC, which reports the amount of Hb in the blood, is always helpful for diagnosing anemia.

Statistical analysis

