The complete analysis dataset will consist of all the anemic patients with no missing values for any parameters in the dataset. The primary variables include MCHC, MCV, RDW, and MCHC. All the data will be summarized for the PBS and automated hematology analyzer results of the anemic patients. Demographic variables will be presented using frequencies and percentages for categorical data and means and standard deviations for continuous data. Outcome variables for continuous data will be analyzed and summarized with maximum, mean, minimum, standard deviation, standard error, and a 95% confidence interval for parametric data. Continuous outcome variables will first be tested for normality using the Kolmogorov-Smirnov test at a 5% significance level (p≤0.05). To compare the results of CBC and PBF methods, data will be evaluated finding the sensitivity, specificity, positive predictive value (PPV), negative predictive value (NPV), and accuracy for both methods. If the data is normally distributed, a paired t-test will compare the means of related groups (CBC group with positive and negative cases). If the data is not normally distributed, the Mann-Whitney test will be used. However, the PBS group with positive and negative cases will be evaluated using the chi-squared test or McNemar's test. This analysis will determine the more effective diagnostic method.

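### Chi-squared is left open as a test between two methods read on the same blood sample, although it does not validly compare paired calls

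*Protocol article*

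**What the plan says.** All of this is in the protocol article, under Materials and methods.

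- **Design.** In Data collection procedure, one EDTA tube per patient goes to the analyzer, and "a blood smear will be prepared in a Blue Star slide (75 mm length, 25 mm width, 1.35 mm thickness) from the given blood sample". Every patient therefore contributes one analyzer reading and one smear reading.
- **Tests, first mention.** The same section says of the two methods' results that "the data will be compared and analyzed by using tests like the paired t-test and chi-squared test to draw a conclusion". McNemar's test does not appear there.
- **Tests, second mention.** Statistical analysis says that "the PBS group with positive and negative cases will be evaluated using the chi-squared test or McNemar's test". It gives no rule for choosing between the two.
- **Purpose.** The sentence that follows is "This analysis will determine the more effective diagnostic method". Earlier in the section, the comparison of methods is framed through accuracy measures for each method: "To compare the results of CBC and PBF methods, data will be evaluated finding the sensitivity, specificity, positive predictive value (PPV), negative predictive value (NPV),". Overall accuracy completes that list.

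**The concern.** Two readings of one sample are matched pairs. The plan recognises this for means, where it names a paired t-test, but does not carry it through to categorical calls. Chi-squared and McNemar's test are not alternatives for such data, because they answer different questions or rest on different variance assumptions. The text ties this analysis to the choice of the better method, so an unsuitable test here bears directly on the study's conclusion.

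The direction of the error depends on how chi-squared is run. Applied to the two positive rates side by side, it can miss a real systematic shift between the methods. That matters when the Abstract already expects the two to match, because a missed difference would read as agreement. Applied to the cross-table, it returns a very small p-value whenever the methods agree better than chance, and this could be misread as a difference between them.

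**Working it through.** **The plan's own figure.** The only computed figure is the sample size: n = 1.96² × 0.286 × (1 − 0.286) / 0.05² = 313.79, rounded up to 314. It reproduces. It is a precision calculation for a single proportion and does not involve the paired comparison.

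**Inputs.** From the article: N = 314, a two-sided 5% level, and one sample read by both methods. Assumed, because the article does not give them: each method's positive rate for an anemia type, and how closely the methods agree.

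**Layout 1: the two positive rates side by side.** Let p be the common positive rate and d the proportion of discordant patients.

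- Unpaired SE of the difference = √[2p(1 − p)/N].
- Paired SE at equal rates = √[d/N].
- Ratio = √[2p(1 − p)/d].

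At p = 0.60 and d = 0.10 the ratio is √(0.48/0.10) = 2.19. Over agreement of 80% to 95% and positive rates of 50% to 60%, it runs from √(0.48/0.20) = 1.55 to √(0.50/0.05) = 3.16.

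In terms of the within-patient correlation ρ at equal rates, d = 2p(1 − p)(1 − ρ), so the ratio is 1/√(1 − ρ). A simulation of 200,000 replicates with N = 314 gave:

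| ρ | SE ratio, equal rates | Chi-squared rejects, both rates 28.6% | McNemar rejects, both rates 28.6% | Chi-squared power, 28.6% v 35.6% | McNemar power, 28.6% v 35.6% |
|---|---|---|---|---|---|
| 0 | 1.00 | 5.0% | 5.0% | 47% | 46% |
| 0.3 | 1.20 | 1.9% | 5.0% | 46% | 61% |
| 0.5 | 1.41 | 0.6% | 5.0% | 45% | 76% |
| 0.7 | 1.83 | 0.04% | 5.0% | 44% | 94% |

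The unpaired test is right only at ρ = 0, which is implausible for two readings of one sample. Above zero it is conservative and loses power.

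**Layout 2: the method-by-method cross-table.** Here chi-squared tests whether the two calls are associated. Take 160 patients positive on both, 15 on the analyzer only, 15 on the smear only and 124 on neither (314 in all). Both methods call 175/314 positive, so there is no difference between them. Chi-squared is 204, with p of about 10⁻⁴⁶. In the simulation with equal rates it rejected in at least 99.9% of trials once ρ was 0.3 or more.

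**One table under each test.** Suppose 80 both positive, 10 analyzer only, 25 smear only and 199 both negative (N = 314):

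- Chi-squared on 90/314 v 105/314: 1.67, p = 0.196.
- McNemar: (10 − 25)²/(10 + 25) = 225/35 = 6.43, p = 0.011 (exact p = 0.017).
- Chi-squared on the cross-table: 174.3, p < 0.001. This tests association only.

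A second table (163, 25, 6, 120) shows the same pattern: 188/314 v 169/314 gives chi-squared p = 0.126, while exact McNemar on 25 v 6 gives p = 0.0009.

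**The case against.** The strongest reply is that the Statistical analysis section, which governs, already names McNemar's test, and that the Data collection wording is an illustrative list whose other member is a paired test. This stands in part. The plan does not fix chi-squared as its comparison, and the authors were not blind to pairing. What remains is that an unsuitable test is named in both places and offered without condition beside the suitable one.

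The article also does not say how chi-squared would be laid out, and the sentence in Statistical analysis attaches it to the smear group alone. A reader might infer that 314 pairs would be analysed as 628 independent patients. That follows only if the positive rates are set side by side; on the cross-table the fault is a different one. A test confined to the smear could not decide between the methods, so a between-method comparison is the sensible reading of a garbled sentence.

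A reader might also infer that the analyst may pick the test after seeing the results. The article does not say when the choice is made, and a separate analysis plan, not shown here, could settle it. That charge is not supported.

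Finally, McNemar's test on calls does not show which method is more accurate. This is correct, and it limits what the fix can achieve.

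**Conclusion.** The point holds as a defect of wording that should be corrected. The calls are paired, and the plan permits a test that does not validly compare them under either layout.

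The size is conditional. For positive rates side by side, the standard error is about 2.2 times too large if 60% are positive and 10% discordant, and 1.5 to 3.2 times too large over 80% to 95% agreement and 50% to 60% positive. For a true 7-point difference, power is 45% against 76% at a correlation of 0.5, and 44% against 94% at 0.7. None of these rates or correlations is in the article.

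Two stronger conclusions are not supported. Under the side-by-side layout, false positives are not inflated. Nor can it be said that a real shift would be reported as no difference, because that depends on the true difference and the agreement. The sample size of 314 is untouched.

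**What to change.** 1. In Statistical analysis, delete chi-squared as a between-method test. Make McNemar's test the only test for paired binary calls, applied to each anemia type, and report the paired difference in proportions with its 95% confidence interval. If the marginal distributions over the three types are compared together, use the Stuart-Maxwell test.
2. In Data collection procedure, align the list of tests with that choice.
3. State that the test shows whether one method systematically calls a type more often than the other, and does not by itself show which is more accurate. The closing sentence of Statistical analysis should be worded accordingly.

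The cost is a few sentences of text. No new data are needed, and the stated sample size does not change.

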## Materials and methods

Study design* *

This cross-sectional study was carried out in the Central Laboratory Department of Pathology at Acharya Vinoba Bhave Rural Hospital, affiliated with Datta Meghe Institute of Higher Education and Research (Deemed to be a University), located in Sawangi, Wardha, Maharashtra, India. The study commenced following the receipt of participants' consent and has been approved by the Institutional Ethics Committee of Datta Meghe Institute of Higher Education and Research (approval number: DMIHER (DU)/IEC/2024/157). It was also registered with the Clinical Trials Registry of India (CTRI/2024/04/066473) (Appendices). A minimum of 314 eligible participants were involved, and the study spanned one year to ensure comprehensive data collection.

Participants

Patients of Indian origin aged 11-65 years diagnosed with anemia will be included. Exclusion criteria include patients diagnosed with leukemia, lymphoma, or other blood disorders as well as those under 11 or over 65 years of age. Patients with chronic kidney disease and liver disease will be excluded as these diseases affect the production of RBS and the indices of erythropoiesis. Patients who are on chronic medications which are known to alter the morphology of RBCs including chemotherapy will also be excluded. Those patients, who were transfused with blood within the last three months, will be excluded from the study since it may shift their RBC parameters slightly.

Data collection procedure

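### The 314 is sized to estimate anemia prevalence, which an all-anemic study does not estimate, so its 5% error does not describe the accuracy measures to be reported

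*Protocol article*

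**What the plan says.** All references are to the protocol article.

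- **Sample size.** Cochran's formula is applied by "considering the proportion of the estimated prevalence of anemia (p=28.6%) from the reference article and the estimation error (d = 5"%). The error is repeated as "E (error of margin) is equal to 5% or 0.05", the multiplier is 1.96, and the worked line ends "resulting in 313.7 or 314 patients needed in the study". The section treats the result as a count of anemic patients: "calculating the total number of anemic patients visiting the hospital, the population size (N) of 314 patients is needed in the study".
- **Participants.** "Patients of Indian origin aged 11-65 years diagnosed with anemia will be included". There is no non-anemic comparison group.
- **Statistical analysis.** The analysis set is limited to anemic patients with complete data. To compare the two methods, "data will be evaluated finding the sensitivity, specificity, positive predictive value (PPV"), the negative predictive value and accuracy are to be found for both. Table 1 in the Results section lists the same measures, with one row each.
- **Results.** The stated aim is to learn whether the histogram can diagnose microcytic, macrocytic and normocytic anemia, with the peripheral blood smear (PBS) as reference.

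No expected sensitivity or specificity, type mix or precision target for the accuracy measures enters the sample size calculation.

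**The concern.** A prevalence formula answers this question: how many people, not selected for anemia, must be examined to estimate the anemic proportion to within 5 points? In this study that proportion is 100% by eligibility. The calculation also counts a different kind of person from those enrolled: 314 unselected people at 28.6% would include about 314 × 0.286 = 90 with anemia, whereas the plan takes all 314 to be anemic.

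The measures that are reported have other denominators. Without non-anemic patients, specificity for anemia as such cannot be estimated. Sensitivity and specificity therefore have meaning only for each type against the smear. A type's sensitivity rests on the patients who have that type, and its specificity on those who do not. Neither count enters the calculation.

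What is at stake is stated precision, not bias. The 5% is the only precision figure in the article, and it belongs to a quantity the study does not estimate. The Statistical analysis section nevertheless expects the analysis to settle which method is more effective, so the precision of the accuracy measures matters.

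**Working it through.** **Inputs from the article:** p = 0.286, E = 0.05, z = 1.96, n = 314 (Sample size); anemic patients only (Participants, Statistical analysis); three types (Results). **Assumed, because the article gives none:** the share of each type and the true sensitivity and specificity. The half-widths take all 314 as analysed; the complete-case rule could leave fewer, and the Study design section calls 314 a minimum.

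**1. The plan's own figure.** n = z² p(1 − p)/E² = 1.96² × 0.286 × 0.714 / 0.05² = 313.79, rounded up to 314. The figure reproduces. In reverse, 1.96 × √(0.286 × 0.714 / 314) = 0.050, so the 5 points apply to a 28.6% proportion measured in all 314.

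**2. Sensitivity for one type.** With m patients of that type and sensitivity s, the 95% half-width is 1.96 × √(s(1 − s)/m). At s = 0.85, s(1 − s) = 0.1275:

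| Assumed share | m | Half-width at 85% |
|---|---|---|
| 50% | 157 | 5.6 points |
| 30% | 94 | 7.2 points |
| 10% | 31 | 12.6 points |
| 5% | 16 | 17.5 points |

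The last two are approximate. With 16 patients only 0.15 × 16 = 2.4 misses are expected, and the normal formula is poor there.

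At other values with a 50% share (157 patients), the half-width is 6.3 points at 80% and 1.96 × √(0.09/157) = 4.7 points at 90%.

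**3. Patients of one type needed for 5 points.** 1.96² × s(1 − s)/0.0025 gives 246 at 80%, 196 at 85%, 139 at 90% and 73 at 95%. As a share of 314 these are 78%, 62%, 44% and 23%.

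**4. A bound that needs no assumed share.** Three types share 314 patients, so the smallest has at most 104 (314/3 = 104.7). A half-width of 5 points or less then requires s(1 − s) ≤ 0.0025 × 104 / 3.8416 = 0.0677, that is, s of about 0.93 or more (for sensitivities above one half).

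**5. Measures that do reach 5 points.**
- Overall accuracy uses all 314: at 85%, 1.96 × √(0.1275/314) = 3.9 points; at 80%, 4.4. The worst case, at 50%, is 5.5.
- Specificity for a type uses the patients without it. At 85% and a 30% share, 314 − 94 = 220 patients give 1.96 × √(0.1275/220) = 4.7 points. At a 10% share, 283 patients give 4.2.

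**The case against.** The best defence is that the article never says a sensitivity will be known to within 5 points. The 5% appears only as an input to Cochran's formula. A reader might infer that the plan promises 5 points for every type's sensitivity, but no sentence does so. This stands, and it limits the point: the stated margin belongs to another quantity, and the accuracy measures are left without one.

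Second, the per-type reading is inferred. Table 1 has one sensitivity row, and the analysis text speaks only of positive and negative cases. That also stands as a caution. The inference is still sound, because the stated aim names three types and the sample contains no one without anemia. The Discussion also describes a cited 354-sample study by sensitivity and specificity for each type.

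Third, a reader might infer that only whole-sample agreement can reach 5 points, or that 314 is simply too few. Neither follows. Specificity for a less common type reaches 5 points at 85%, and so does sensitivity of 90% in a type making up half the sample. For a type's sensitivity the margin is not assured; it is not impossible.

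Fourth, a reader might take 314 to be an arithmetic error, because the general formula as printed lacks the factor p. The worked line includes p and gives 314, so this is probably a typesetting slip and no part of the point.

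Last, enrolment and analysis would not change. That is correct and lowers the seriousness, but the justification is still for the wrong quantity.

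**Conclusion.** The point stands as a mismatch between the sample size justification and the study's measures. The arithmetic behind 314 is correct; the quantity it was computed for is fixed by eligibility and is not estimated. The 5% error therefore does not describe the accuracy results.

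The practical shortfall is confined mainly to the sensitivity of the less common types. The least common of three types misses 5 points unless its sensitivity is about 93% or more, whatever the mix. Beyond that bound the size depends on assumptions: at 85% sensitivity, from 5.6 points with a 50% share to roughly 12 to 18 points with shares of 10% to 5%. Overall accuracy and the specificity of less common types are adequately served by 314 at the values examined. The estimates are not biased by this. It should be fixed, but it does not call the design or the enrolment target into question.

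**What to change.** Keep 314. In the Sample size section, remove anemia prevalence as its justification and state instead the precision that 314 gives for overall accuracy and for each type's sensitivity and specificity. Show this over a stated range of assumed type shares and true values, labelled as assumptions, and do not present 5% as the margin for the study's results. Example wording: with 314 patients and a true value of 85%, overall accuracy is estimated to within about 4 points; the sensitivity of a type making up 50%, 30% or 10% of patients to within about 6, 7 and 13 points; and the specificity of a type making up 30% to within about 5 points. Add the corresponding figures at 80% and 90%. Say explicitly that sensitivity and specificity are calculated by type against the smear, if that is the intention.

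The cost is one rewritten paragraph. No further patients are needed, so the change is possible even if enrolment is complete. The stated precision becomes less favourable for the sensitivity of the rarer types.

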
Limitations

Lack of Morphological Detail

RBC histograms do not provide information on cell shape or other morphological abnormalities, which are often crucial for diagnosing conditions like spherocytosis or sickle cell anemia. This can necessitate additional testing with a PBS or other diagnostic methods.

Calibration Dependency

The accuracy of RBC histograms is highly dependent on the proper calibration and maintenance of the hematology analyzer. Calibration drift can lead to erroneous results, which is less of a concern with manual PBS.

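### The complete-case analysis set can drop usable patients and hide non-results, which may overstate accuracy by an amount the documents leave open

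*Protocol article*

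**What the plan says.** The Statistical analysis section of the protocol article sets the analysis population in one sentence: "The complete analysis dataset will consist of all the anemic patients with no missing values for any parameters in the dataset". No other analysis set is defined. The same paragraph then lists the measures to be computed: "data will be evaluated finding the sensitivity, specificity, positive predictive value (PPV), negative predictive value (NPV), and accuracy for both methods".

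Under Data collection procedure, MCV, MCH, MCHC and RDW all come from one analyser run on one EDTA tube, and one pathologist reads the smear made from the same sample. The Results section treats the smear as the traditional method against which the histogram is judged, for microcytic, macrocytic and normocytic anemia.

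The Sample size section derives the target from a single-proportion formula, "resulting in 313.7 or 314 patients needed in the study", and the Study design section states "A minimum of 314 eligible participants were involved". The article says nothing about smears that cannot be read, analyser runs that give no usable result, or samples that cannot be assigned a type.

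**The concern.** In a comparison of two diagnostic methods, a missing result need not be a clerical gap. If a method gives no usable answer for a patient, that is part of how it performs. A rule that keeps only fully complete records takes such a patient out of the denominators for both methods. The accuracy table could then look the same for a method that always gives an answer and for one that often does not.

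The rule also asks for more than the comparison needs. To compare anemia type, a patient needs a type from the analyser and a type from the smear. A patient with both but no recorded MCHC, for example, contributes all the information the comparison uses and is still excluded.

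At stake is the stated purpose of the analysis, which is to decide which method is more effective. If the excluded samples are the difficult ones, the reported accuracy describes an easier set of patients than the one enrolled.

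**Working it through.** **1. The plan's own figure.** Inputs from the Sample size section: "is the level of significance at 5%, i.e., confidence interval is equal to 1.96" and "p is equal to 28.6% or 0.286, and E (error of margin) is equal to 5% or 0.05".

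n = z² × p × (1 − p) / E² = 1.96² × 0.286 × 0.714 / 0.05² = 313.79, rounded up to 314.

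The stated 314 reproduces (the printed 313.7 is a truncation). The calculation contains no allowance for exclusions.

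**2. Effect of the rule on accuracy.** Let A be accuracy among complete cases, m the share of patients excluded, and b the accuracy the excluded patients would have had. Then

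- accuracy in all patients = A(1 − m) + b·m
- overstatement = A − [A(1 − m) + b·m] = m(A − b)

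The documents give none of these quantities, so all are assumptions: A = 90%, m from 2% to 10%, and three values of b. Overstatement in percentage points:

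| Excluded, m | b = 90% (as good as the rest) | b = 70% (harder samples) | b = 0 (all count as failures) |
|---|---|---|---|
| 2% | 0 | 0.4 | 1.8 |
| 5% | 0 | 1.0 | 4.5 |
| 10% | 0 | 2.0 | 9.0 |

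If the excluded samples were easier (b = 95%), the sign reverses, with an understatement of 0.1 to 0.5 points.

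**3. The two kinds of non-result must be kept apart.** Because the smear is the reference for the histogram, an unreadable smear is a missing reference result, not a histogram error. Illustration (assumed numbers): 314 patients, 16 without a complete pair, and 268 of the remaining 298 in agreement.

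- Complete cases: 268/298 = 89.9%.
- All 16 counted against the histogram: 268/314 = 85.4%, a gap of about 4.6 points.
- If 8 of the 16 are unreadable smears, only the other 8 are histogram failures: 268/(298 + 8) = 268/306 = 87.6%, a gap of about 2.4 points.

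Pooling the two kinds of failure roughly doubles the apparent effect in this example.

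**4. How many patients the rule could remove.** Take six items: four indices, the histogram and the smear result. With independent missingness of 1% or 2% on each (assumed), 314 × 0.99⁶ = 296 or 314 × 0.98⁶ = 278 remain. Independence is doubtful, because the indices and histogram come from one run. If these fail together, there are two sources of loss, and 314 × 0.99² = 308 or 314 × 0.98² = 302 remain. The number lost therefore depends strongly on how missingness clusters.

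**The case against.** The strongest reply is that the article never mentions unreadable smears or failed runs. It does not say they would be recorded as missing or that they arise in harder samples. Their removal is an inference from the rule, and if missingness is unrelated to classification the bias is zero. That stands, and it is why the point is worded as a possible bias with a range that starts at zero.

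It can also be said that 'parameters' probably means laboratory measurements. The article uses the word that way elsewhere and speaks separately of demographic variables. A reader might infer that a blank demographic field removes a patient; the wording does not clearly support that. The point does not need it, since a single missing index is enough, although indices from one run will often be missing together.

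Two stronger readings are tempting and should not be drawn:

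- *The analysed number must fall below 314.* The Study design section gives 314 as a minimum of participants, so enrolling more could absorb losses. A shortfall follows only if enrolment stops at 314, which the article does not say.
- *The 5% margin for accuracy is lost.* That margin was set for an anemia prevalence of 28.6%, not for sensitivity, specificity or accuracy. Even on its own terms, with exactly 314 enrolled, the half-width moves only from 5.00 to 5.13 points at 5% loss and 5.27 at 10%.

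The remark on calibration drift under Limitations does not bear on this point. Drift produces wrong values, which remain in the dataset.

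Finally, coding rules for indeterminate results are commonly left to a full protocol or SAP. That would answer a complaint about silence. Here the article commits to a specific rule, and a SAP that followed it would inherit the problem.

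**Conclusion.** The concern holds as a selection problem. The only stated analysis set is a complete-case set over all parameters. It can discard patients with both classifications, and it can hide non-results of either method from the accuracy comparison. Upward bias is possible but not established. Under the assumptions in the working, it runs from 0 to 2.0 points if excluded samples classify between 90% and 70%, and from 1.8 to 9.0 points if every exclusion counts as a failure. The last range is an upper case for the histogram, because some exclusions would be missing reference smears. Without a documented rate of non-results, no single figure can be defended.

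Loss of precision is not part of the conclusion. What remains on sample size is that the article does not say whether 314 is the number enrolled or the number analysed.

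**What to change.** - Base the histogram-versus-smear comparison on all eligible patients with both classifications, whether or not other parameters are present. Summarise each index on the patients who have it.
- Add a 'not classifiable' result for each method, distinct from a blank field, and report its frequency and reasons by method. Enter it when the sample is read, because a blank may not later show whether the test failed or the entry was missed.
- Report histogram accuracy twice: excluding the histogram's own non-results, and counting them as failures among patients with a readable smear.
- Report unreadable smears separately as missing reference results, not as histogram errors.
- State whether 314 is the enrolled or the analysed number.

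The cost is a change of analysis wording and one extra result code. Reported accuracy may be slightly less favourable. If data entry has already closed (the article mixes past and future tense), the reasons for blanks would have to be recovered from laboratory records where possible.
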